### Data-analysis

Descriptive analysis on all the patient characteristics at baseline is performed. A t-test for independent groups will be used to check for comparability between the intervention and control group at baseline. A repeated-measures multivariate analysis of variance (MANOVA) will be applied to assess possible effect of increased therapeutic time over various test moments (baseline, 8 weeks and at the moment of discharge). The level of significance is 0.05. The SPSS-PC version no. 20 will be used for data-analyses (SPSS Inc., Chicago, IL, USA).

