**Methods:**

A comparative single blind controlled study will be applied. Patients suffering from a stroke and staying on one of the rehabilitation units of the nursing homes are eligible for participation. Participants belong to the intervention group if they stay in two nursing homes where four interventions of the Clinical Nursing Rehabilitation Stroke Guideline were implemented. Participants who stay in two nursing homes where therapy is given according to the Dutch stroke Guideline, are included in the control group. Clinical neuropsychologists will assess patients’ cognitive functioning, level of depression (mood) and anxiety. Nurses will assess a Barthel Index score on a weekly basis (ADL). These variables are measured at baseline, after 8 weeks and at the moment when participants are discharged from the nursing home.

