## Methods

### Study design

The design of the study is a single blind controlled trial with two patients groups coming from nursing homes with two different rehabilitation approaches. The study consists of an effect evaluation and will be carried out in four nursing homes in the Netherlands. In the two control nursing homes, rehabilitation is only performed by therapists and based on the Dutch Stroke Guidelines [17]. Consequently, therapy time will be limited. In two intervention nursing homes, exercises derived from the Clinical Nursing Rehabilitation Stroke Guideline [34], are an additional part of the rehabilitation program, resulting in an extra 50 minutes a day of exercises for the patients.

The Medical Ethical Committee of the Free University Amsterdam, The Netherlands, approved this study.

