### Study population

Patients suffering from a stroke will be eligible for participation, even if they suffer from co-morbid diseases such as heart disease, recurrent stroke or pre-existing depression. Patients will be excluded if they will leave the rehabilitation unit within two weeks, when they are too ill to participate, if there is a language problem, like aphasia, or when a Mini-Mental State Examination (MMSE) [35] score is lower than 13. A score of 13 or higher is a prerequisite for a neuropsychological assessment. Patients will be recruited by the head of the nursing staff, working on the rehabilitation unit of the nursing homes. Oral and written information about the study is given to the patients and/or their legal representatives. Prior to their participation in the study oral and written informed consent will be acquired from all the participants, their family or legal representatives. Informed consent will be based on veracity, anonymity, privacy, and confidentiality.

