### Randomisation

A convenience sample will be taken of patients who rehabilitate in the selected nursing homes in the period of April 2012 until April 2015 and are willing to participate.

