### Outcome measures

#### Patient characteristics

The following background characteristics are measured in both patient groups: age, gender, level of education, marital status, living situation, smoking and drinking alcohol.

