### Medical history data

Type of stroke, TIA, Parkinson, disorders of consciousness, brain tumor, epilepsy, alcohol or other abuse, depression and or psychiatric problems and medication. Medication use is coded according to the guideline of the Dutch Pharmacotherapeutic Compass [36].

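### The arms are non-randomised convenience samples from different homes, but the stated analysis is a baseline t-test and a repeated-measures MANOVA with no covariate named

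*Protocol article*

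**What the plan says.** **Allocation.** The Abstract's Methods define the arms by place of stay: "Participants belong to the intervention group if they stay in two nursing homes where four interventions of the Clinical Nursing Rehabilitation Stroke Guideline were implemented", and "Participants who stay in two nursing homes where therapy is given according to the Dutch stroke Guideline, are included in the control group". Study design says that the study "will be carried out in four nursing homes in the Netherlands", so there are two homes per arm. The section headed Randomisation describes no random allocation: "A convenience sample will be taken of patients who rehabilitate in the selected nursing homes".

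**Recruitment.** Under Study population, "Patients will be recruited by the head of the nursing staff, working on the rehabilitation unit of the nursing homes". The Single-blind section says that homes, patients, caregivers and treating teams know the treatment.

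**Data collected.** Patient characteristics lists "age, gender, level of education, marital status, living situation, smoking and drinking alcohol". Medical history data lists "Type of stroke, TIA, Parkinson, disorders of consciousness, brain tumor, epilepsy, alcohol or other abuse, depression and or psychiatric problems and medication". Procedure has the nursing staff score the Barthel Index every week.

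**Analysis.** Data-analysis gives three steps: a descriptive analysis of the baseline characteristics, the statement that "A t-test for independent groups will be used to check for comparability between the intervention and control group at baseline", and a repeated-measures MANOVA over baseline, 8 weeks and discharge at the 0.05 level. It names no covariate, no other adjustment method, and no action if the t-test finds a difference.

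**Acknowledged limitation.** The Discussion lists possible selection bias from the convenience sample and offers no analysis to deal with it.

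**The concern.** When the home decides the arm, differences in case mix are to be expected and not merely possible. The Background itself treats case mix as prognostic: it says that impaired cognition and low mood go with poorer functional recovery and that depressed patients recover less well. Study population nevertheless admits patients with pre-existing depression, heart disease or an earlier stroke. If one pair of homes takes in more such patients than the other, recovery will differ between the arms whatever therapy is given.

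The stated plan has two defences. The first is the t-test, which can only fail to find a difference and has no stated consequence. The second is that baseline is one of the MANOVA test moments, so the group-by-time comparison cancels a gap that stays constant. Neither deals with a factor that changes the rate of recovery. Run as written, the analysis would report such a difference as an effect of extra therapy time, and the Discussion intends positive results to guide policy makers and practitioners.

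**Working it through.** **Inputs from the article** (Sample size and Data-analysis): planned effect d = 0.30; 69 per arm before the dropout allowance; 81 per arm to be enrolled; level 0.05. Sidedness is not stated, so two-sided is assumed. The article gives no figure for the comparability check, so there is none to reproduce. The two sample sizes are used as printed, and the point does not depend on how they were derived.

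**Step 1. What the t-test can detect.** For a true imbalance δ in SD units and n per arm, the test statistic is noncentral t with 2n − 2 degrees of freedom and noncentrality δ√(n/2).

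- n = 69, δ = 0.30: noncentrality 0.30 × √34.5 = 1.76, critical value 1.978 on 136 df, power 0.417, so missed 58% of the time.
- n = 81, δ = 0.30: noncentrality 0.30 × √40.5 = 1.91, critical value 1.975 on 160 df, power 0.475, so missed about 52% of the time.

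| True imbalance | Power, 69 per arm | Power, 81 per arm |
|---|---|---|
| 0.20 SD | 21% | 24% |
| 0.30 SD | 42% | 48% |
| 0.40 SD | 65% | 72% |

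The imbalance detected with 80% power is about (1.96 + 0.84) × √(2/n): 0.48 SD at 69 per arm and 0.44 SD at 81. A baseline check runs on those enrolled, so the column for 81 is the natural one if recruitment reaches target.

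**Step 2. What an unadjusted imbalance does to the estimate.** The bias in the group-by-time effect is approximately

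bias = (imbalance in SD) × (correlation of the factor with change in the outcome).

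The article gives neither quantity, so both are assumptions. The bias is set against d = 0.30 as if on the same SD scale.

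| Imbalance | Correlation 0.3 | Correlation 0.5 |
|---|---|---|
| 0.2 SD | 0.06 SD (20% of d) | 0.10 SD (33%) |
| 0.3 SD | 0.09 SD (30%) | 0.15 SD (50%) |
| 0.4 SD | 0.12 SD (40%) | 0.20 SD (67%) |

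**Step 3. Effect on the error rate.** In a simple two-group comparison with 69 per arm and no true effect, a bias of 0.09 SD raises the nominal 5% rejection rate to about 8%, and a bias of 0.15 SD raises it to about 14%. This is an illustration and not the exact MANOVA error rate.

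**Step 4. What baseline as a test moment covers.** Suppose the arms differ by a constant c in the outcome at every occasion. The group-by-time contrast subtracts c from itself and the gap disappears. Suppose instead that a factor X adds an amount to the change, and X differs between arms. That amount stays in the contrast in full unless X, with its own effect on change, is in the model.

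**The case against.** **A condensed article leaves covariates to the analysis plan.** This is the strongest point. A reader might infer that the collected factors are never to enter the model. The article does not say so; it only names none, and a fuller plan could add them. What stands is that Data-analysis does more than stay silent: it names the comparability check and the effect model, and that pair is inadequate for a comparison that was not randomised.

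**The baseline t-test is not the only protection.** True. Baseline is a MANOVA test moment, and the exclusions (MMSE below 13, aphasia, too ill, leaving within two weeks) narrow the case mix. Neither removes differences in recovery among those who remain.

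**Other readings that go beyond the text.**

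- That the head nurse hand-picks patients. The article says that this person recruits, under stated criteria, from those willing to take part. Unblinded recruitment into a convenience sample is supported; deliberate selection is not.
- That t-tests will be run on gender, marital status, living situation or stroke type. The t-test sentence does not say which variables it covers and may mean continuous ones only.
- That an undetected 0.30 SD imbalance would by itself produce the whole planned effect. A covariate imbalance is not a bias of the same size; Step 2 scales it by the association with change.

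**The limitation is disclosed.** It is, but disclosure leaves the estimate unchanged.

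**Conclusion.** The concern holds in this form: for non-randomised arms, the stated analysis contains nothing that removes differences in recovery due to measured case mix, although data to reduce them are being collected. The t-test cannot fill the gap. It would miss a 0.30 SD imbalance about 58% of the time at 69 per arm and about 52% at 81, and nothing follows from its result. These figures rest on a two-sided 5% test and the article's sample sizes.

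The possible bias, 0.09 to 0.15 SD or 30% to 50% of the planned effect, rests on an assumed 0.3 SD imbalance and assumed correlations of 0.3 to 0.5 with change. It shows what is plausible and does not predict the actual bias.

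It would also be wrong to infer that adjustment makes the comparison as good as randomised. With two homes per arm, patient-level covariates cannot separate the effect of treatment from that of the homes.

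**What to change.** In Data-analysis:

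1. Replace the t-test as the comparability check with standardised differences for all baseline factors, reported without a significance test.
2. Name the adjustment set in advance and use it whatever the differences show: age, gender, education, stroke type, depression history and baseline Barthel Index. All are already collected. Stroke recurrence and stroke date are not itemised as collected, so they should not be assumed available.
3. Choose one treatment of baseline. Either keep it as a test moment and include covariate-by-time terms, so that the factors can affect change, or use the baseline outcome as a covariate and analyse only the later occasions. It cannot serve in both roles. For the Barthel outcome, its baseline enters once only. The two approaches can give different answers when the groups are not equivalent, so the choice must be made before the data are seen.
4. State that adjustment reduces measured case-mix bias only, that home and treatment effects remain inseparable with two homes per arm, and limit the conclusions accordingly.

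**Cost:** a few degrees of freedom, a rule for missing covariate values, and a more guarded conclusion. No new data collection is needed.

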The question arises whether an increase in exercise time of approximately 50 minutes a day is sufficient to have a beneficial influence on cognition, e.g. executive functions, and mood in frail stroke patients. It is known that a decline in cognition and mood both relate to more severe functional limitations and less functional recovery [25,26]. More specifically, the prevalence of cognitive disorders in stroke patients is high and varies from 22% [27] to 63% [28]. It has been observed that cognitive impairment after stroke influences recovery of functional outcome and activities of daily living negatively in older stroke survivors [29,30]. Concerning mood, the frequency of e.g. depression after stroke is also high (33%) [31]. Depressed patients have poorer recovery patterns and need more time to achieve a high level of independence [32]. Moreover, stroke patients who could not successfully being discharged from nursing homes were more depressed [33].

In sum, the primary goal of the present study is to investigate whether an increase in therapy time has a beneficial influence on the various dimensions of cognition of frail stroke patients at discharge of rehabilitation units of nursing homes. The secondary goal is to examine whether an increase in therapy time improves mood, resulting in an improvement in activities of daily living (ADL).

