### Effect evaluation

#### Primary outcome measures cognition

##### Assessment of cognition

Cognition will be assessed by the following neuropsychological tests:

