### Global cognitive functioning

#### Mini-mental state examination

Global cognitive functioning will be assessed by the Mini-Mental State Examination (MMSE). MMSE is a brief screening test and has been developed to screen for cognitive impairment, which has a joint reliability of 0.95 in a study of patients with various neurological disorders [35].

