### Executive functions

#### Behavioural assessment of dysexecutive syndrome

##### Rule Shift Cards

A subtest of the BADS [37] is the Rule Shift Cards (BADS-RS), which is meant to assess set-shifting. This subtest discriminates people with an executive dysfunction from healthy people. Participants have to respond to stimuli (red or black playing cards) according to two rules that are presented consecutively. The maximum score is 4.

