##### *Key-search test*

Another subtest of the BADS is the Key-search test. This test assesses the executive sub functions planning and problem-solving. The goal is to choose a systematic, and efficient strategy to find a key lost in a field. The inter-rate reliability of the BADS varies from 0.88-1.00. Brain injured patient achieve significant lower scores on the test which suggest that construct validity of these tests is as good as that of established tests [37]. The maximum score is 4.

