#### Category fluency

Set-shifting, one of the executive functions, will be assessed by Category Fluency [38,39]. This test requires shifting from one category of names to another category. This test uses the category ‘animals’, test re-test reliability 0.82, and professions, test re-test reliability 0.96.

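### Eight cognitive tests are all primary and no deciding result is fixed; read one by one at 0.05, the chance of a false positive is up to about 34%

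*Protocol article*

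**What the plan says.** The Background of the protocol article gives the primary goal: to find out whether more therapy time "has a beneficial influence on the various dimensions of cognition of frail stroke patients at discharge". The outcome section is headed "Primary outcome measures cognition" and opens with "Cognition will be assessed by the following neuropsychological tests". The tests that follow are:

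- MMSE
- Rule Shift Cards (BADS)
- Key-search (BADS)
- Category Fluency
- Eight words test
- Face Recognition (RBMT)
- Picture Recognition (RBMT)
- MOCA

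That makes eight tests. Category Fluency is described with two categories: "This test uses the category ‘animals’, test re-test reliability 0.82, and professions, test re-test reliability 0.96". Counted apart, they make nine scores. No test is put first and no composite is defined. Mood has its own secondary heading and ADL follows it, so the primary list ends with the MOCA.

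The Sample size section uses one effect size (0.30), alpha 0.05, power 0.80, two groups and three measurements, and arrives at 138 patients, 69 per group. The Data-analysis section plans a repeated-measures MANOVA over the three test moments. Its one statement on error control is "The level of significance is 0.05".

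**The concern.** A primary outcome should tell the reader, before any data are seen, which result will count as the answer. Here the answer could be a joint test, any one of eight or nine scores, a group effect or a group-by-time effect, and the article does not choose among them. One alpha and one effect size suggest a single primary test, while the outcome list and the goal (several dimensions of cognition) suggest many.

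The Abstract and the Discussion say that positive effects would guide policy makers and practitioners. As the text stands, a claim that extra therapy time improves cognition could be built on whichever test happened to reach significance.

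**Working it through.** **The plan's own figure.** The stated inputs are effect 0.30, alpha 0.05, power 0.80, two groups and three measurements. The stated result is 138 in total.

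- Two-mean formula, n per group = 2(z_alpha + z_power)²/d². Two-sided: 2(1.960 + 0.842)²/0.30² gives 175 per group. One-sided: 2(1.645 + 0.842)²/0.30² gives 138 per group, which equals the stated number only as a per-group figure, not as a total.
- Repeated-measures F test with f = d/2 = 0.15 and m = 3 measurements. The noncentrality is N·m·f²/(1 + (m − 1)ρ) for the group effect and N·m·f²/(1 − ρ) for the interaction. Total N is 120 and 146 at ρ = 0, 142 and 130 at ρ = 0.1, and 236 and 74 at ρ = 0.5.

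So 138 arises only near ρ = 0.05 to 0.1, and the article states neither ρ nor the metric of the effect. The figure cannot be confirmed. What matters here is that the number of tests is not among the stated inputs.

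**Reading 1: each test judged separately at 0.05.** For k independent tests with no true effect, P(at least one false positive) = 1 − 0.95^k.

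- k = 8: 1 − 0.95^8 = 0.337
- k = 9: 1 − 0.95^9 = 0.370
- Favouring the intervention only, k = 8: 1 − 0.975^8 = 0.183

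The tests will be correlated, and the article gives no correlations. Assumed equal correlations r were simulated with 400,000 draws of k null z-statistics, counting |z| > 1.96 (or z > 1.96 for the favourable direction):

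| r (assumed) | 8 tests, either direction | 8 tests, favourable only | 9 scores, either direction |
|---|---|---|---|
| 0 | 34% | 18% | 37% |
| 0.3 | 30% | 15% | 33% |
| 0.5 | 25% | 13% | 27% |
| 0.7 | 19% | 9% | 20% |
| 0.9 | 12% | 6% | 12% |

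**Reading 2: one joint MANOVA on all tests.** If no test is affected, the chance of a false positive is 5%. But a significant joint test says only that some combination of scores differs between groups. The goal asks for a beneficial effect on dimensions of cognition, so test-by-test follow-up is needed and Reading 1 returns at that step. The sample size inputs do not include the number of dependent variables, on which the power of a joint test depends.

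**What adjustment would cost.** Take the stated 80% power at 0.05 at face value. Bonferroni over eight tests (also Holm's first step) uses 0.05/8 = 0.00625, z = 2.734.

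- Power per test: Φ(1.960 + 0.842 − 2.734) = Φ(0.068), about 53%.
- Patients needed to hold 80%: (2.734 + 0.842)²/(1.960 + 0.842)² = 1.63 times as many; 69 × 1.63 gives about 113 per group before dropout.

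**The case against.** The strongest reply is that the Data-analysis section names a multivariate analysis, in the singular, and attaches 0.05 to it. A reader might infer that each of the eight tests is judged at 0.05, so that the 5% level fails for the primary question. The text does not say so, and under one joint MANOVA the level is held when nothing is affected. This objection stands against that inference. It does not settle what decides the primary question, because the article does not list what enters the MANOVA and a joint test cannot supply a direction or a dimension.

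Second, a reader might infer that a chance positive on cognition is likely. The figures do not support that word. The tests overlap (the MMSE is global, and the MOCA covers executive functions and memory), so independence gives the upper end. In the favourable direction the range for eight tests is 18% down to 6%.

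Third, follow-up tests and multiplicity adjustment are commonly left to an analysis plan, and only a condensed article is shown. That is fair, and the missing adjustment is not itself the point. Naming the deciding primary result and the quantity the trial is sized for is a protocol matter. The article does address both, with an unranked list and a single effect. If an unseen plan adjusts over eight tests, the stated sample size would not carry that adjustment.

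Fourth, a composite is not the only sound answer. It can hide opposite effects on executive function and memory, and it does not report on each dimension. That also stands, and the fix therefore offers a choice.

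**Conclusion.** The concern holds in a limited form: the result that decides the primary question is not fixed. Eight tests share primary status without order, one effect size is used for the sample size, and one 0.05 is not assigned to any particular test. Read separately, the eight tests carry a false-positive chance of up to about 34%, falling to 25% and 19% at correlations of 0.5 and 0.7, and roughly half of that in favour of the intervention. Read jointly, the level is 5%, but the result does not answer the stated goal and is not what the sample size describes.

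The figures rest on assumed equal correlations and on each single test holding its own 5% level. The list itself is plain on the page; which of the two readings was meant cannot be told from the article.

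**What to change.** Before the data are analysed, state one deciding analysis for cognition at discharge, the time point in the primary goal, and name the contrast to be tested.

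- **One option:** a composite z-score, the mean of the listed executive and memory tests standardised to baseline, tested at 0.05, with the individual tests reported under Holm adjustment. State whether the MOCA, which spans both domains, enters the composite. The MMSE, already the entry screen, could be descriptive.
- **Alternative:** keep all tests primary, apply Holm across them, and state whether fluency counts as one score or two.

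In either case, say which outcome the 0.30 refers to, and restate the power if it does not apply to the chosen analysis.

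The cost is wording, plus a revised power statement where needed; no new data are required. Single-test results carry less confirmatory weight, a composite can mask opposing effects across domains, and the Holm route lowers power per test as shown above.
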